### Statistical analysis

2.8

#### Sample size

2.8.1

With an alpha error of 5% (2-sided test), a power of 80%, an intraclass correlation coefficient of 0.8 and a mean difference of bacteria counts between the two caries risk groups of 1,300,000, a total of 200 sites, meaning 50 subjects, needs to be selected.

#### Analysis

2.8.2

Three main steps will be realized: preparation of descriptive summaries, modelling using a mixed (linear) model and correlating bacterial abundances. A mixed linear model for the log-count abundance of each species at a measured site will be used to test for potential effects of gender, interdental space and the location of each site. Two categorical variables (site location and gender), and one numerical variable (interdental space) will be modelled as fixed effects and one categorical variable will be modelled as a random effect (subject). This random effect will be included to model correlation between the four interdental sites of a given study participant. In the regression, each coefficient will be tested according to the null hypothesis which indicates that the coefficient is zero when a likelihood-ratio test is applied. The p-values less than 0.001, 0.05, and 0.01 will be respectively considered strong, medium and low evidence with respect to the null hypothesis. To perform the correlation analysis and avoid over-estimating the inter-site correlation, the residuals of the model described above will be used. The trees associated with the correlation plot will be generated by hierarchical cluster analysis with complete linkage. Other multivariate analyses, such as factor analysis, will be used to graphically check the correlations between bacteria quantification and all potential caries risk factors. A multilevel logistic regression analysis will finally be performed to test which oral characteristics are significantly linked with the two caries risk groups. The linear mixed effects modelling package, lme4 [21] in R environment [22] will be used to generate all statistical analyses and associated plots.

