### Repartition of subjects according to caries risk conditions

2.4

The American Academy of Pediatric Dentistry [3] sets out criteria which will be used, with certain modifications, to classify patients according to their carious risk (Table 1). The low carious risk subjects presented Caries Protective Terms, i.e., brushing daily with fluoridated toothpaste and regular dental care, Caries Risk Indicators, i.e., socio-economic status (medium, high) and snacking (low, medium) and Clinical Indicators, i.e., less than one interproximal lesion and no enamel defects nor active white spot lesions and adequate saliva flow rate. The high carious risk subjects presented Caries Protective Terms, i.e., no daily brushing with fluoridated toothpaste and/or irregular dental care and/or Caries Risk Indicators, i.e., low socio-economic status and high snacking and/or Clinical Indicators, i.e., more than one interproximal lesion and/or active white spot lesions and/or enamel defects and/or inadequate saliva flow rate.

**Table 1 tbl1:** Adolescent caries risk assessment.

FACTORS	HIGH RISK	LOW RISK
Biological (interview)		
- Patient with low socioeconomic status	Yes	No
- Patient has >3 between meal sugar-containing snacks or beverages per day	Yes	No
Protective (interview)		
- Patient brushes teeth daily with fluoridated toothpaste	No	Yes
- Patient has regular dental care	No	Yes
Clinical Findings (International Caries Detection and Assessment System (ICDAS) and salivary tests)		
ICDAS		
- Patient has >1 interproximal lesion	Yes	No
- Patient has active white spot lesions or enamel defects	Yes	No
Salivary tests (hydration, salivary consistency, resting saliva pH, stimulated saliva flow, stimulated saliva pH and saliva buffering capacity)		
- Patient has high salivary risk	Yes	No

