### Microbiological analysis

2.7

Quantification of the total number of bacteria and 26 pathogens will be performed by real-time PCR. The pathogens selected periodontal or carious bacteria: *Actinomyces odontolyticus, Aggregatibacter actinomycetemcomitans, Bifidobacterium dentium, Campylobacter rectus, Campylobacter gracilis, Capnocytophaga ochracea, Clostridium cluster IV, Clostridium cluster XIV, Eikenella corrodens, Fusobacterium nucleatum, Lactobacillus* spp.*, Parvimonas micra, Porphyromonas gingivalis, Prevotella intermedia, Prevotella nigrescens, Rothia dentocariosa, Scardovia wiggsiae, Streptococcus cristatus, Streptococcus mitis, Streptococcus mutans, Streptococcus salivarius, Streptococcus sanguinis, Streptococcus sobrinus, Tannerella forsythia, Treponema denticola,* and *Veillonella parvula.* Simplex quantitative real-time PCR assays will be performed in a volume of 10 μL (2 μL of DNA extract, 1 × SYBR® Premix Ex TaqTM Tli RNaseH Plus and 1 μM of each primer) (TaKaRa, Shiga, Japan).

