In some CRA classifications, the quantification of *S. mutans* in the saliva is considered [3]. However, the results concerning the link between *S. mutans* and the development of dental caries is not clear. Some studies demonstrated a real association between *S. mutans* and the carious lesion whereas others revealed no clear association [29]. Moreover, the amount of *S. mutans* needed to initiate the carious lesion varies according to the study [30]. Recent studies revealed that the decrease of the taxonomy and the presence of key pathogens are signals preceding the carious disease [31,32]. The issue of one pathogen could be integrated with the interdental microbiota taxonomy variation. Thus, to use *S. mutans* or other bacteria as a biomarker in the CRA classification, it is necessary to identify specific biomarkers associated with carious lesions and to normalize their quantification. For this, the MIARC study had the advantage of an extensive sample of interproximal sites. Moreover, although the list is not exhaustive, the bacteria identified by the real-time PCR technique correspond mainly to those identified in the current literature as being potentially at cariogenic risk.

As we will focus on interdental microbiota, results should be more significant and correlated to the carious risk. The real-time PCR method presents the advantage of quantifying bacteria specifically. Furthermore, comparatively speaking, this method is straightforward, economical and reliable [33].

Recent progress achieved in understanding the “systems biology” of dental caries has broadened the research beyond individual factors (e.g., fluoride content, salivary pH, or measuring quantities of bacterial species) and has established a platform for the advancement of innovative approaches in caries diagnosis and management [34]. This advancement will certainly be facilitated by the development of innovative applications to monitor biomarkers and manifestations of disease as they occur.

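### Total bacterial load is measured but not used, so the residual species correlations carry plaque quantity, and absolute counts alone cannot separate more plaque from different plaque in a risk-group comparison

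*Protocol article*

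**What the plan says.** Section 2.7 of the protocol article: "Quantification of the total number of bacteria and 26 pathogens will be performed by real-time PCR". Section 2.6 takes these samples site by site, one brush per interdental site, so total load should be available for each site.

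Section 2.8.2 sets the outcome as "A mixed linear model for the log-count abundance of each species at a measured site" and lists the covariates: "Two categorical variables (site location and gender), and one numerical variable (interdental space) will be modelled as fixed effects". Subject is the only random effect. Total load appears neither as denominator, offset nor covariate. The correlations between bacteria, and the clustering drawn with them, are computed on the residuals of this model.

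Caries-risk group is not a term in the mixed model. It enters in a later step: "A multilevel logistic regression analysis will finally be performed to test which oral characteristics are significantly linked with the two caries risk groups". The predictors of that regression are not listed. Factor analysis and similar methods are also planned, to relate bacterial quantities graphically to caries risk factors.

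Section 2.4 builds brushing into the groups. Low risk requires "brushing daily with fluoridated toothpaste and regular dental care". High risk can be reached by "no daily brushing with fluoridated toothpaste and/or irregular dental care and/or Caries Risk Indicators" and by clinical indicators.

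The Discussion says that, before bacteria are used as biomarkers in caries risk assessment, "it is necessary to identify specific biomarkers associated with carious lesions and to normalize their quantification". It closes by expecting to learn whether the interdental microbiota differs between the two groups and to find a specific marker for each.

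**The concern.** The count recovered from a brush is the product of two things: how much biofilm was present and picked up, and what share of it belongs to the species. On the log scale these add. Load is common to every species in the same sample, so a model without it leaves a shared component in every species' residual. The correlation plot and its tree would then partly show biofilm quantity while being read as ecological association. Interdental space and site location absorb load only as far as load follows gap size and position.

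The same ambiguity reaches the risk groups. If the high-risk group carries more plaque of identical composition, absolute counts of many species rise together. The conclusion sought, a marker specific to a risk level, needs the two explanations separated.

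**Working it through.** **What can be taken from the protocol.** 25 subjects per risk group (50 subjects at a 1:1 ratio, section 2.3), 4 sites each, intraclass correlation 0.8 and two-sided alpha 0.05 (section 2.8.1), and 26 targets (section 2.7). The protocol gives no figure for load, for its variation or for any species' SD. The sample size supplies none either: 200 sites is stated without an SD, so it cannot be reproduced. Solved backwards with design effect 1 + 3 × 0.8 = 3.4, it implies an SD of about 1.78 million on the raw count scale, which does not convert to a log SD. All SDs, fold differences and shares of non-brushers below are therefore assumptions.

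**Residual correlation.** Write log10 count = L + S, with L the log load common to all species in a sample and S the species' log relative abundance, independent between species. Then

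r = SD(L)² / (SD(L)² + SD(S)²).

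With SD(L) = 0.4:
- SD(S) = 0.3: 0.16 / (0.16 + 0.09) = 0.64
- SD(S) = 0.4: 0.16 / (0.16 + 0.16) = 0.50
- SD(S) = 0.8: 0.16 / (0.16 + 0.64) = 0.20

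Simulation with no load difference between groups gave mean r of 0.63 (SD(S) = 0.3) and 0.20 (SD(S) = 0.8).

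If subject effects are removed and L and S both have intraclass correlation 0.8, each variance is multiplied by 0.2 and the ratio is unchanged: 0.032 / (0.032 + 0.018) = 0.64 and 0.032 / (0.032 + 0.128) = 0.20. If the two intraclass correlations differ, the value moves, but it is zero only if load does not vary between sites of one mouth.

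**One species compared by risk group, composition unchanged.** A subject mean of 4 sites has variance σ²(0.8 + 0.2/4) = 0.85σ². The standard error of the group difference is σ√(2 × 0.85/25) = 0.261σ. For σ = 0.7 this is 0.183. A 2-fold load gives log10(2) = 0.301, or 1.65 standard errors; a 3-fold load gives 0.477, or 2.61. Probability of p < 0.05 if the whole high-risk group is shifted:

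| σ (log10) | 2-fold | 3-fold |
|---|---|---|
| 0.5 | 0.62 | 0.95 |
| 0.7 | 0.37 | 0.73 |
| 1.0 | 0.20 | 0.43 |

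**26 species, with only some of the high-risk group not brushing.** Simulation with SD(L) = 0.4, no compositional difference, and a group test on subject means. Mean number of species with p < 0.05 on absolute counts:

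| Load in non-brushers | All non-brushers, SD(S) 0.3 / 0.8 | 40% non-brushers, SD(S) 0.3 / 0.8 |
|---|---|---|
| 1-fold | 1.3 / 1.3 | 1.3 / 1.2 |
| 1.5-fold | 6.9 / 2.9 | 2.2 / 1.5 |
| 2-fold | 16.3 / 6.2 | 3.7 / 2.1 |
| 3-fold | 24.5 / 13.5 | 6.9 / 3.1 |
| 5-fold | 26.0 / 21.8 | 12.1 / 5.3 |

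Chance alone gives 26 × 0.05 = 1.3. The log ratio to total load gave 1.2 to 1.3 in every row. That is close to automatic here, because the simulated total is error-free and composition has no group effect. It shows what the adjustment removes, not how it would perform with a noisy total.

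**The case against.** The strongest objection is that the mixed model contains no risk term. A reader might infer that, as planned, more plaque in high-risk non-brushers makes every species look like a biomarker. The protocol does not support that. This model cannot flag any species by risk. The predictors of the logistic regression are not given and may include total load, and leaving them to a fuller document is no defect in an article. Not brushing daily is one of several alternative criteria, so a daily brusher can be high risk. Section 2.3 excludes regular users of interdental brushes, floss or mouthwash from both groups and requires sites free of bleeding and inflammation, which may narrow any difference in load. No load difference is documented. With a 2-fold load, 40% non-brushers and SD(S) = 0.8, the excess is small: 2.1 species against 1.3 by chance.

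A reader might also infer that the plan breaks its own normalisation requirement. The Discussion sentence follows a remark that the amount of *S. mutans* needed to start a lesion varies between studies. It can equally mean standardising measurement, and it does not mention total load.

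Absolute abundance is also a legitimate target. The aim is to quantify, and load may itself be part of caries risk.

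Finally, residuals from a model with a subject effect might be thought to remove load. They remove most of the between-subject part. The site-to-site part remains and is still shared by all species.

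All of this stands except the last point, which does not clear the residual correlations.

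**Conclusion.** The point holds in two parts.

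1. The residual correlations are a defect in what is written, since section 2.8.2 states the outcome scale and lists the fixed effects, and load is not among them. Under the assumed SDs, unrelated species would correlate at about 0.20 to 0.64, with no difference between risk groups needed.

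2. For risk groups the point is conditional. If absolute counts enter those analyses, or a risk term is added to the mixed model, a quantity difference and a compositional shift cannot be told apart. The size ranges from negligible (1.5 of 26 species, against 1.3 by chance) to all 26, depending on load differences and non-brusher shares that the protocol does not give.

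Modelling absolute counts is not wrong in itself. What is missing is a load-adjusted result beside it, and the trial already collects the data for that. The absent risk term is a separate matter.

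**What to change.** Keep the absolute-count analysis. For each species add a load-adjusted analysis, with log(species count / total count) at the same site as outcome or log total count as covariate, in two places: the risk-group comparisons and the model whose residuals feed the correlation plot and tree. Report both sets. Describe a species as a specific, compositional marker only when the load-adjusted result supports it, and otherwise as a difference in bacterial quantity.

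The cost is one further model per species and a second set of estimates; no new data are needed. Ratios have limits of their own: a rise in a dominant species lowers the ratios of the others, and measurement error in the total is shared by all ratios from that sample. The adjusted results therefore supplement the absolute counts and do not replace them.

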### Interdental microbiota sample

2.6

Four interdental sites (15–16, 25–26, 35–36, and 45–46), free from caries (ICDAS code 0), will be assessed for each subject. The adapted interdental brush (Curaden, Kriens, Switzerland) will be determined by using a Curaprox IAP calibration probe (Curaden) [18]. Then, the isolation of each tooth selected for sampling will be performed by using sterile dental cotton rolls and a calibrated, sterile interdental brushes (IDB) will serve to remove the interdental biofilm. The IBDs containing the individual samples will be stored in sterile tubes at 4 °C for later laboratory treatment [19,20].

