Thus, the MIARC trial allows one to evaluate if carious pathogens are present in the interdental space of adolescents and to determine if the interdental microbiota of adolescents with a high carious risk is different from the one of adolescents with a low carious risk. This should allow one to determine a specific biomarker of each carious risk. This quantification of determined bacteria could be added to CRA to improve them. This study should help optimize recommendations in terms of oral prevention in this at-risk age group. Furthermore, the expected results will provide new information on the association between the level of carious risk, measurement of the state of oral hygiene, clinical signs of gingival inflammation, diameter of the interdental spaces and interdental microbiota composition.

In conclusion, the MIARC study is a first step before further studies, ideally longitudinal clinical studies encompassing large populations which would identify the panel of bacteria as prospective oral health markers. With this new data, oral health professionals will be able to collect and analyse interdental microbiota to prevent the risk of new caries.

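### The species log-count mixed model has no caries-risk-group term, so it cannot estimate or test the high-versus-low-risk count difference on which the trial is sized

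*Protocol article*

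**What the plan says.** Section 2.8.2 of the protocol article describes a mixed linear model for the log-count of each species at each site. The model "will be used to test for potential effects of gender, interdental space and the location of each site". The terms are then enumerated: "Two categorical variables (site location and gender), and one numerical variable (interdental space) will be modelled as fixed effects", and subject is the one random effect. Likelihood-ratio tests apply to the coefficients of that regression.

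Section 2.8.1 sizes the trial on a different contrast: "a mean difference of bacteria counts between the two caries risk groups of 1,300,000". It gives its other inputs as "With an alpha error of 5% (2-sided test), a power of 80%, an intraclass correlation coefficient of 0.8" and concludes that "a total of 200 sites, meaning 50 subjects, needs to be selected". Section 2.3 sets the high-to-low risk ratio in the enrolled population at 1.0. The Introduction names the association of the microbiota with carious risk as the secondary outcome. The Discussion says the trial allows one to "determine if the interdental microbiota of adolescents with a high carious risk is different from the one of adolescents" at low risk.

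The remaining steps in section 2.8.2 are descriptive summaries, a correlation analysis on residuals of the same model, factor analysis used graphically, and a closing multilevel logistic regression of the two risk groups on oral characteristics, which are not defined.

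**The concern.** The list of fixed effects is closed and counted, so leaving out risk group cannot be put down to a condensed description. An analyst who follows section 2.8.2 would fit models with no high-versus-low coefficient. The power statement would then refer to a test that the count model does not contain. The trial could finish with tests of gender, site and interdental space for every species, but with no estimate or interval for the difference in counts by caries risk. That difference is the only comparison given a power calculation.

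**Working it through.** **Inputs.** From section 2.8.1: two-sided alpha 0.05, power 80%, "an intraclass correlation coefficient of 0.8", difference 1,300,000 on the raw-count scale, 200 sites in 50 subjects. From section 2.6: four sites per subject. From section 2.3: 1:1 by risk, hence 25 per group. No SD of the counts is given.

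**Step 1: match each planned analysis to the sized contrast.**

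| Analysis in section 2.8.2 | Does risk group enter? | Gives a high-minus-low count difference? |
|---|---|---|
| Descriptive summaries | not stated | no test |
| Mixed model per species | no | no |
| Correlation of residuals | no | no |
| Factor analysis | risk factors, graphically | no |
| Multilevel logistic regression | yes, as outcome | no; at most a log odds of high risk per unit of a predictor |

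**Step 2: the plan's own figure.** Without an SD, N = 50 cannot be reproduced; it can only be inverted.

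- Design effect = 1 + (4 − 1) × 0.8 = 3.4.
- Effective sites = 200 / 3.4 = 58.8, or 29.4 per group.
- Standardised difference at 80% power = (1.960 + 0.842) × √(2 / 29.4) = 0.73.
- Implied SD = 1,300,000 / 0.73 ≈ 1.78 million.
- Other readings: 1.64 million if one value per subject is analysed, and 3.28 million if clustering is ignored.

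Range over assumed SDs, with the design effect of 3.4:

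| Assumed SD | Subjects for 80% power | Power with 50 subjects |
|---|---|---|
| 1.5 million | 36 | 91% |
| 1.75 million | 50 | 81% |
| 2.0 million | 64 | 70% |
| 3.0 million | 144 | 38% |

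The sample size is therefore consistent with a two-group comparison that allows for clustering, at an SD near 1.78 million.

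**Step 3: where the group difference goes when the term is missing.** Risk group is constant within a subject, so a shift of δ between two equal groups is taken up by the subject random effect and raises its variance by about δ²/4. With δ = 0.73 this is 0.73² / 4 = 0.13. In 200 simulated trials (25 subjects per group, four sites, total variance 1, ICC 0.8, gender balanced, interdental space unrelated to group) the mean estimated subject variance was 0.90 without the term and 0.76 with it. The gap of about 0.14 is close to 0.13.

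**Step 4: what adding the term gives.** In the same 200 trials, the likelihood-ratio test of the group term at 5% rejected in 78%. The Monte Carlo standard error is √(0.78 × 0.22 / 200) = 0.03, so this agrees with the planned 80%. The mean estimated effect was 0.72 against a true 0.73. The number of subjects did not change.

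**The case against.** The strongest reply is that risk group is tested elsewhere. The closing logistic regression does name the two groups, and the text does not exclude bacterial counts from oral characteristics. Since the Discussion hopes for a biomarker of each risk level, including them is a natural reading. A reader might infer from the mixed model that the group comparison is never tested at all; the article does not support that, because an association between counts and group may be tested in the reverse direction. What stands is narrower. The predictors are undefined, and an odds ratio for group membership is neither the mean difference in section 2.8.1 nor what its 80% power refers to. It would also be tempting to call the logistic model unworkable, because group does not vary within a subject. The article does not state its unit of analysis or random-effect level, so that cannot be concluded here.

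Second, the Introduction puts identification and quantification of the microbiota first and association with risk second. For the first aim, a model with site, gender and interdental space is reasonable. This tempers the point but does not remove it, because the risk-group difference is the contrast that was sized.

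Third, a reader might infer that the correlation analysis is also spoiled. If its residuals are conditional on the subject effect, the random intercept already removes most of any group shift: with ICC 0.8 and four sites the shrinkage factor is 3.2 / 3.4 = 0.94, which leaves about 6%. That is minor.

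Finally, an unseen analysis plan might add the term. The finding, however, is not missing detail: the article fixes a complete list of terms that does not fit its own sample-size basis.

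**Conclusion.** The point holds. As written, the log-count mixed model has no risk-group coefficient in any of the 26 species models, so it cannot estimate or test the difference on which 50 subjects and 80% power rest. No other described analysis estimates that difference; the logistic regression may test an association, but not this one. The omission itself follows from the stated terms and needs no numerical assumption.

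The size of the remedy does rest on assumptions. The figure of about 78% power uses a back-solved effect of 0.73 SD, ICC 0.8 and normal errors on the analysis scale. Section 2.8.1 is on raw counts while the model is on log counts, so neither the 80% nor the 78% is guaranteed for the log-scale test.

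**What to change.** In section 2.8.2:

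- Add caries risk group (high/low) as a fixed effect in each species' mixed model. Keep gender, site location and interdental space as fixed effects and the subject random intercept.
- Report the risk-group coefficient with its 95% CI, back-transformed to a ratio of geometric mean counts, as the risk-group comparison.
- Say which count the 1,300,000 in section 2.8.1 refers to. If it is total bacteria, fit the same model to the total count.
- State that section 2.8.1 is on the raw-count scale, so its 80% power does not transfer exactly to the log-scale test.
- Say which oral characteristics enter the logistic regression and whether bacterial counts are among them.

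The cost is one term in models already planned, possibly one further model for the total count, and a few sentences. No additional subjects, sites or assays are needed, since risk group is already determined for every subject at enrolment.

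### The single interdental-space coefficient blends a within-mouth and a between-adolescent slope; splitting it into two terms is a cheap improvement

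*Protocol article*

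**What the plan says.** Section 2.8.2 (Analysis) models the log-count of each species at a measured site. The model "will be used to test for potential effects of gender, interdental space and the location of each site". On its form the text is specific: "Two categorical variables (site location and gender), and one numerical variable (interdental space) will be modelled as fixed effects". Subject is the only random effect, included to carry the correlation among an adolescent's four sites. For testing, "each coefficient will be tested according to the null hypothesis which indicates that the coefficient is zero when a likelihood-ratio test is applied". Neither caries risk nor oral hygiene is among the fixed effects of this model.

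Section 2.6 samples four interdental sites per adolescent and chooses the brush with a calibration probe. I read interdental space as a site-level measurement on that basis.

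The Discussion (section 3) expects the results to be informative about an "association between the level of carious risk, measurement of the state of oral hygiene, clinical signs of gingival inflammation, diameter of the interdental spaces and" the composition of the microbiota. It does not say whether the diameter part is meant between sites within a mouth or between adolescents.

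Section 2.8.1 (Sample size) assumes "an intraclass correlation coefficient of 0.8" for 200 sites in 50 subjects. That figure accompanies a difference in bacteria counts, whereas the model uses log-counts.

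**The concern.** A variable measured at several sites per person carries two comparisons. One is wider against narrower sites in the same mouth. The other is adolescents with generally wide spaces against those with generally narrow ones. A random-intercept model with one coefficient averages the two slopes by the information in each. The average describes both comparisons only if the slopes are equal, that is, only if diameter is unrelated to the subject effect.

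The document gives some reason for doubt. The sample size rests on "a mean difference of bacteria counts between the two caries risk groups of 1,300,000", so subject-level differences in counts are expected, and caries risk is not in this model. If diameter goes with caries risk, hygiene or another subject-level factor, part of that association enters the interdental-space coefficient. A small p-value could then be read as an effect of space at the site when there is none. A reader interested in differences between adolescents would meanwhile see only a diluted version. The same model is fitted species by species, so the ambiguity recurs across the panel of 26.

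**Working it through.** **The plan's own figure.** 200 sites cannot be reproduced forwards, because the article gives no SD. Backwards: design effect 1 + (4 − 1) × 0.8 = 3.4; effective sites per group 100/3.4 = 29.4; SD = 1,300,000 × √(29.4/2)/(1.960 + 0.842) ≈ 1.78 million, a standardised difference of about 0.73. The point here does not depend on this; 0.73 is used only in the caries-risk check below.

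**Inputs from the article.** 50 subjects, 4 sites each, ICC 0.8, two-sided 5% (section 2.8.2 grades p-values at three cut-offs; 5% is used here), likelihood-ratio test, location and gender as fixed effects.

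**Assumed inputs, not in the article.** The share τ of diameter variance that lies between adolescents: 0.2, 0.5, 0.8. The correlation r between an adolescent's underlying diameter and the subject effect on log-count: 0, 0.4, 0.6. The ICC ρ of 0.8 is carried over from counts to log-counts, then varied.

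**Step 1: weight of the between-adolescent slope in the pooled coefficient.**

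- Between information: I_B = (50 − 2) × [τ + (1 − τ)/4] / [ρ + (1 − ρ)/4]
- Within information: I_W = (50 − 1) × 3 × (1 − τ)/(1 − ρ)
- Weight = I_B/(I_B + I_W)

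At ρ = 0.8:

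| τ | I_B | I_W | Weight |
|---|---|---|---|
| 0.2 | 48 × 0.40/0.85 = 22.6 | 147 × 0.8/0.2 = 588 | 0.037 |
| 0.5 | 48 × 0.625/0.85 = 35.3 | 147 × 0.5/0.2 = 367.5 | 0.088 |
| 0.8 | 48 × 0.85/0.85 = 48 | 147 × 0.2/0.2 = 147 | 0.246 |

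At ρ = 0.5 the weights are 0.116, 0.246 and 0.526; at ρ = 0.2 they are 0.246, 0.449 and 0.735. The blend therefore shifts with two variance ratios that have nothing to do with the biological question.

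**Step 2: rejection rates by simulation.** Random-intercept model fitted by maximum likelihood, 1,000 trials per setting, true within-mouth slope zero, ρ = 0.8. Monte Carlo error is about 1 point at 13%: √(0.13 × 0.87/1000) = 0.011. The settings share random numbers, so the within column is one estimate repeated.

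| r | τ | Pooled | Split: between | Split: within |
|---|---|---|---|---|
| 0 | 0.2 / 0.5 / 0.8 | 4.9 / 5.2 / 5.4% | 6.8 / 6.6 / 6.7% | 4.9% |
| 0.4 | 0.2 / 0.5 / 0.8 | 6.5 / 13.2 / 29.1% | 50.5 / 72.4 / 80.4% | 4.9% |
| 0.6 | 0.2 / 0.5 / 0.8 | 9.3 / 21.0 / 59.5% | 87.3 / 97.9 / 99.3% | 4.9% |

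The between term is slightly liberal under the null, so its rejection rates are a little flattered.

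**Step 3: other outcome ICCs, r = 0.4.** At ρ = 0.5 the pooled test rejects 10.6–47.5% and the split between term 44.4–72.8%. At ρ = 0.2 the figures are 12.9–40.3% and 30.0–51.1%.

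**Step 4: a purely within-mouth effect** (0.12 SD of log-count per SD of diameter, ρ = 0.8). Pooled against split within term: 83.2% v 83.1% at τ = 0.2, 63.6% v 66.9% at 0.5, and 26.7% v 32.5% at 0.8. Splitting costs essentially nothing here.

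**Step 5: slopes of opposite sign** (r = −0.4 with that same within slope). At τ = 0.8 the pooled test rejects 6.2%, the between term 78.4% and the within term 32.5%. The two slopes largely cancel in the pooled coefficient.

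**Step 6: caries risk as the only link.** With the back-solved difference of 0.73 and assumed diameter differences between risk groups of 0.5–1.5 subject-level SD, the pooled test rejects about 4–15% and the split between term about 10–35%. The larger figures in step 2 need further subject-level factors, such as hygiene.

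**The case against.** The strongest reply is that the stated target is site-level and the pooled coefficient already comes close to it. At an ICC of 0.8 the within-mouth slope carries 1 − 0.246 = 75% to 1 − 0.037 = 96% of the weight, and step 4 shows almost no loss for a true within-mouth effect. That stands, and it limits the harm.

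A reader might go further and infer three things that the article does not support.

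- **That the study promises a between-adolescent association of diameter with microbiota, which this test would miss.** The Discussion names no level. Section 2.8.2 also plans multivariate analyses and a multilevel logistic regression for the links with caries risk, so that part does not rest on this coefficient.
- **That the coefficient answers neither question.** Step 4 contradicts this for the site-level one.
- **That the test both over-rejects badly and is nearly blind.** These are one rejection rate read in two ways. At τ = 0.2 it hardly sees the between-adolescent association (6.5%) and hardly over-rejects; at τ = 0.8 it does more of both (29.1%). No single loss of power can be quoted, because τ and r are not in the article.

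It is also fair to say that a condensed article may leave centring to a fuller plan. But the text is not silent: it names one numerical variable and a test of each coefficient. Finally, leaving caries risk out of the model is a separate matter. Adding it would remove one source of correlation between diameter and the subject effect, but not the others.

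**Conclusion.** The point holds as a cheap improvement, not as a serious flaw. The stated model gives interdental space one coefficient whose meaning depends on two slopes being equal, and nothing in the article secures that.

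The size is conditional. Under a zero within-mouth slope, r = 0.4 and an outcome ICC of 0.8, the pooled test rejects about 6.5–29%, where a clean site-level test would reject about 5% and a clean between-adolescent test about 50–80%. With r = 0 there is no distortion, and through caries risk alone the distortion is modest. Interdental space is also not among the aims in the Introduction, which concern the microbiota and its association with carious risk.

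**What to change.** In section 2.8.2, replace the single interdental-space term with two:

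1. the adolescent's mean interdental space over the four sites;
2. each site's deviation from that mean.

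Test and report both coefficients. Base the site-level statement on the deviation term, which subject-level factors cannot confound, whether measured or not. Base any between-adolescent statement on the mean term, described as an association, since that term remains open to confounding by caries risk and hygiene. State in the Discussion which level the diameter association refers to. The residuals used for the correlation analysis would then come from the revised model.

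Cost: a sentence or two of text and one extra parameter per species model, from data already planned. The between-adolescent estimate will be less precise because it rests on 50 subjects, and its likelihood-ratio test runs slightly above 5% at that size (6.6–6.8% at an ICC of 0.8).
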